## 8.2 SECONDARY ENDPOINTS

EFFICACY ENDPOINTS

1. Food challenge test scores at the age of 28 weeks
2. Total IgE antibody titer in serum at the age of 28 weeks
3. Egg white, ovomucoid, milk, soy, wheat, and peanut-specific IgE antibody titers in serum at the age of 28 weeks
4. Egg white, ovomucoid, milk, soy, wheat, and peanut-specific IgG4 antibody titers in serum at the age of 28 weeks
5. Eczema Area and Severity Index (EASI) scores at 2, 4, and 8 weeks after study entry and at the age of 28 weeks
6. Patient Oriented Eczema Measure (POEM) scores weekly through the study
7. Percentage of disease-free days throughout the study
8. Dose of rescue medication used throughout the duration of the study
9. Infants’ Dermatitis Quality of Life Questionnaire (IDQoL) at 2, 4, and 8 weeks after study entry and at 28 weeks of age
10. Family Impact of Childhood Eczema Questionnaire (DFI) at 2, 4, and 8 weeks after study entry and at 28 weeks of age
11. Cumulative incidence of IgE-mediated FA assessed by a doctor’s interview during the study
12. Cumulative incidence of wheezing assessed by a doctor’s interview during the study

Justification for secondary endpoints (efficacy)

(1) Scoring of the food challenge test has already been recommended in the American Academy of Allergy, Asthma & Immunology – European Academy of Allergy and Clinical Immunology PRACTALL consensus report (65).

(2) (3) To evaluate allergy sensitization

(4) To evaluate immune tolerance against hen’s egg

(5) (6) To evaluate the activity and severity of AD

(7) (8) To evaluate the disease control

(9) (10) To evaluate the QoL

(11) To evaluate the prevalence of other IgE-mediated FA except hen’s egg

(12) To evaluate the prevalence of signs related to asthma

SECONDARY ENDPOINTS (SAFETY)

1. Serious adverse events
2. Adverse drug reactions
3. Salivary cortisol concentrations at 2, 4, and 8 weeks after study entry and at the age of 28 weeks
4. Body weight and body height at the age of 28 weeks

Justification for secondary endpoints (safety)

(1) (2) To evaluate safety of the study drugs

(3) To evaluate the effect on adrenal function by adverse drug reactions to TCSs

(4) To evaluate the effect of adverse drug reactions to TCSs on growth

ADHERENCE EVALUATION

(1) TCS adherence index in accordance with the protocol

(2) Dose of TCS used during the study

Justification for adherence evaluations

(1)(2) To evaluate adherence to the protocol

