## 9.2 ANALYSIS SET

The following data set is used for analysis. The target analysis of the primary endpoint of efficacy is defined as Full Analysis Set (FAS).

1. Full Analysis Set (FAS)

The group excluding the participants as follows from all the participants who are randomized

- - Participants who have never received intervention
  - Participants who have not yielded data after the start of the study treatment
  - Participants who are found to have violated eligibility criteria after received intervention t

1. Per Protocol Set (PPS)

Of the FAS, the group consisting of participants without significant deviation from the implementation plan

1. Target group for safety analysis

The group consisting of all participants who have undergone the study treatment at least once

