9.3.3 SECONDARY ENDPOINTS ANALYSIS

All secondary endpoints will be analyzed using FAS and secondarily using PPS. The details of statistical methods are described in the statistical analysis plan.

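### Sections 9.2 and 9.3.3 of the protocol contradict each other on the population for safety: 9.2 defines a safety set, but 9.3.3 sends every secondary endpoint, safety included, to the FAS and PPS

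*Protocol*

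**What the plan says.** Protocol section 8.2 divides the secondary endpoints into efficacy and safety. Under the heading that begins "SECONDARY ENDPOINTS (SAFETY" it lists serious adverse events, adverse drug reactions, salivary cortisol, and body weight and height at 28 weeks of age.

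Section 9.2 defines three analysis sets.
- The FAS starts from all randomised infants and removes, among others, "Participants who are found to have violated eligibility criteria after received intervention" and "Participants who have not yielded data after the start of the study treatment".
- The PPS is "Of the FAS, the group consisting of participants without significant deviation from the implementation plan".
- The third set, called "Target group for safety analysis", is "The group consisting of all participants who have undergone the study treatment at least once".

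Section 9.3.3 then assigns the sets: "All secondary endpoints will be analyzed using FAS and secondarily using PPS". It makes no exception for safety and leaves only the details of statistical methods to the statistical analysis plan. Section 9.3.4 includes safety endpoints in the interim analysis without naming a set for them.

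**The concern.** The safety endpoints are secondary endpoints by the protocol's own classification, so the only sentence in 9.3 that assigns a population to them selects the FAS and then the PPS. The set that 9.2 names for safety receives no endpoint.

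The choice has consequences because the FAS drops some infants who were exposed to study treatment. A safety comparison should describe what happened to everyone exposed, whether or not they should have been enrolled. At least one exclusion criterion bears directly on the risk of harm: criterion 3 in section 4.2, earlier side effects of the study emollient or topical steroids. If such an infant is enrolled in error, treated and then reacts, a FAS safety table leaves out both the infant and the reaction. Section 1.1.3 notes that children are more susceptible to steroids than adults and cites adrenal suppression in 2 of 44 children under proactive treatment, so the safety comparison is a substantive part of this trial.

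**Working it through.** The protocol states no figure on this point, so there is none to reproduce. The check is a comparison of sections, followed by an illustration of size.

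**Step 1. Which endpoints does 9.3.3 cover?** All secondary endpoints. Section 8.2 places the four safety items among them, so 9.3.3 covers safety.

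**Step 2. Is any endpoint assigned to the safety set?** Section 9.3.1 concerns background variables. Section 9.3.2 puts the primary endpoint on the FAS and secondarily the PPS. Section 9.3.3 puts all secondary endpoints on the same two sets. Section 9.3.4 refers the primary endpoint back to 9.3.2 and names no set for safety. No endpoint is assigned to the safety set.

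**Step 3. Who differs between the sets?** From the definitions in 9.2:

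| Infant | FAS | PPS | Safety set |
| --- | --- | --- | --- |
| Never treated | out | out | out |
| Treated, eligible, with data | in | in, unless a significant deviation | in |
| Treated, later found ineligible | out | out | in |
| Treated, no data after treatment start | out | out | in |

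The third row is the one that matters. The PPS is a subset of the FAS, so the secondary analysis cannot bring these infants back. The fourth row affects only the denominator: an infant with a recorded event has yielded data, so removing an infant without data deletes no event.

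**Step 4. How large could it be?** The protocol gives neither the share f of infants treated and later found ineligible nor an event risk r. Both are assumptions here, shown over a range, with the same risk r in the excluded infants as in the rest.

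- Infants outside the FAS: 650 × f.
- Expected events among them: 650 × f × r.
- Chance that at least one event is left out: 1 − (1 − r)^(650 × f).

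| f | 650 × f | Expected events left out, r = 2% | Chance of at least one, r = 1% | r = 2% | r = 5% |
| --- | --- | --- | --- | --- | --- |
| 1% | 6.5 | 0.13 | 6% | 12% | 28% |
| 2% | 13 | 0.26 | 12% | 23% | 49% |
| 5% | 32.5 | 0.65 | 28% | 48% | 81% |

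At r = 2% the whole trial would expect 650 × 0.02 = 13 events, so the expected share left out equals f (0.13/13 = 1%, 0.26/13 = 2%, 0.65/13 = 5%). With equal risk the numerator and denominator shrink together and the expected rate is unchanged. The reported rate is biased downward only if the excluded infants carry above-average risk, which is plausible for criterion 3 but cannot be quantified from the protocol.

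**The case against.** The strongest reply is that the name of the third set is itself an assignment. Section 9.2 introduces its sets as the ones used for analysis and calls one of them the safety set, so a sensible analyst would use it for safety and treat the word *all* in 9.3.3 as loose drafting. This stands in part. It means the protocol has not settled on ignoring the safety set; it contains two instructions that conflict. It does not remove the conflict, because 9.3.3 is the explicit rule. Nor can the matter be left to the statistical analysis plan: 9.3.3 fixes the sets in the protocol, so a plan that used the safety set would contradict it.

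A second reply is that late-discovered ineligibility should be uncommon. Section 5.2 has eligibility confirmed by the physician and checked by the data capture system before assignment. That is fair and is why the effect is probably small. The same section nevertheless provides for misregistration and does not cancel registrations once made.

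A reader might also infer several stronger things that the documents do not support:

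- *That harms would vanish from the record.* Sections 7.3 to 7.3.3 have serious adverse events and drug reactions entered in the chart and eCRF whatever the analysis set, and serious events sent individually to the monitoring committee. Only the tabulated between-group analysis is affected.
- *That a sizeable share of events would be lost, say one or two of the six or seven expected in an arm at 2% risk (325 × 0.02 = 6.5).* With 1% to 3% of an arm excluded, about 3 to 10 infants, the expected loss at 2% risk is 3 × 0.02 = 0.06 to 10 × 0.02 = 0.2 events per arm. Expecting to lose even one event would need a risk of 1/10 = 10% to 1/3 = 33% among the excluded, about 5 to 17 times the assumed rate.
- *That the PPS would drop infants who over-used steroid or changed regimen.* Sections 5.6.4 and 12.2.1 call the change of regimen in the conventional group a deviation, but nothing calls it significant, and nothing says over-use leads to exclusion. Those infants also stay in the FAS.
- *That several exclusion criteria mark steroid risk.* Section 4.2 justifies criterion 4 (recent systemic steroids) by its effect on the primary outcome, and criterion 10 speaks of disease that affects skin evaluation. Only criterion 3 points directly at drug reactions.

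**Conclusion.** The point holds as a contradiction between 9.2 and 9.3.3, and 9.3.3 is wrong as written. Taken literally, it excludes treated infants later found ineligible from the comparative analysis of all four safety endpoints. Because 9.3.4 names no set for safety, the same reading could carry into the interim safety analysis that goes to the monitoring committee.

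The size cannot be stated, because the protocol gives no rate of ineligibility and no rate of harm; the figures above rest on assumed values for both. If few infants are found ineligible after treatment, the effect is small. The correction is worth making because the rule is stated, conflicts with the protocol's own safety set, and is easy to put right.

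**What to change.** Reword 9.3.3 along these lines:

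> Secondary efficacy endpoints will be analysed in the FAS and secondarily in the PPS. The safety endpoints listed in 8.2 (serious adverse events, adverse drug reactions, salivary cortisol, body weight and height) will be analysed in the safety set defined in 9.2, which includes treated infants later found ineligible.

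Add to 9.3.4 that the interim analysis of safety endpoints uses the same safety set. If a statistical analysis plan repeats the wording of 9.3.3, change it there too.

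The cost is about two sentences of text and the approval that a protocol change requires. There are no new data, visits or participants, and the primary analysis and sample size are untouched.

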9.3.4 INTERIM ANALYSIS

Interim analysis is conducted with the aim of preventing disadvantages to participants due to excessive efficacy and safety procedures unintended in study treatment. The interim analysis is performed when almost half of the participants finish their assessments for the primary endpoint. The interim analysis is done for primary endpoint and safety endpoints. The study registration for study participants does not stop while conducting the interim analysis. The analysis of primary endpoint is performed along with 9.3.2 primary endpoints analysis. The stopping boundary for the analysis of primary endpoint will be calculated based on the O’Brien–Fleming type with a Lan–DeMets α and βspending function at the actual information time. For example, the significance levels of effective discontinuation and invalid discontinuation are 0.0015 and 0.2883, respectively, with the interim analysis for 307 participants who are half of the planned study participants. The interim analysis is conducted by a trial statistician of the interim analysis under a closed situation. The statistician prepares a report of interim analysis results and submits it to the independent data monitoring committee. The results of the interim analysis will be evaluated by the members of the independent data monitoring committee to investigate whether or not the study continues, and the investigation result report is submitted to the principle investigator.

# 10 DATA MANAGEMENT

Data management is carried out according to the data management plan determined separately.

# 11 ETHICAL CONSIDERATIONS

This study follows the Declaration of Helsinki Ethical Principles for Medical Research Involving Human Subjects and the Ethical Guidelines for Medical and Health Research Involving Human Subjects (2014 December 22, the Japanese Ministry of Education, Ministry of Health, Labour and Welfare Notification No. 3).

## 11.1 ETHICAL REVIEW

This study is performed with the permission of the dean of each institute after it has been reviewed and approved by each Institutional Review Board (IRB).

## 11.2 INFORMED CONSENT

Prior to the start of the study, the investigators will obtain voluntary written consent from the proxy person (parents or legal guardians) after adequately explaining the explanatory items listed below based on the explanatory document (supplement 5) with obtaining sufficient understanding for the study. The investigators will inform the proxy person (parents or legal guardians) that all participants are free to withdraw at any time from study participation and that the proxy person’s (parents or legal guardians) refusal or withdrawal from participation in the study does not cause any disadvantage to participants. Investigators and the proxy persons’ (parents or legal guardians) sign their names and the date on the consent form when investigators obtain the informed consent. Withdrawing consent never suffers a disadvantage.

Explanatory items

- The title of the study
- The name of the study investigational site and the head of the study
- Purpose and necessity of the study
- Study methods
- Expected participants
- Expected benefits and disadvantages
- Voluntary participation and the right to withdraw
- Share study protocol
- Privacy and confidentiality
- Sample and data management (storage and discard)
- Study funding and conflict of interest
- Communication with participants
- Cost burden and reward
- Matters concerning the case of unapproved (medicine/device) study
- Handling of genetic characteristics and so forth
- Compensation for health damage
- How to deal with samples and data for future study
- Monitoring and audit

## 11.3 WITHDRAWAL OF CONSENT

If the proxy persons (parents or legal guardians) request to withdraw their consent for study participation, investigators will follow the procedure described below (supplement 6).

1. Investigators will collect the consent withdrawal form (supplement 6) from the proxy person (parents or legal guardians) and review the form.
2. Investigators will instruct the study-coordinating center to let the participants withdraw from the study and to discard the samples.
3. The study-coordinating center will instruct the sample storage center to discard the samples.
4. The storage center will inform when the samples have been discarded by completing the form (supplement 7).
5. The study-coordinating center will inform the head investigator of the investigational site by phone or email when the samples have been discarded.

## 11.4 PRIVACY AND CONFIDENTIALTY

Participants’ privacy and confidentiality will be respected throughout the study. The heads of the investigational sites must establish a system of safety management for privacy and confidentiality.

For publication, confidentiality of participants’ identifying information is required. All data can only be used for the study purposes. If the data is supposed to be used for another purpose outside of this study, another informed consent form is required from the proxy person (parents or legal guardians).

Personal information of participants is anonymous (modified and controlled samples and information for any participants which are not be judged by others). The personal information is appropriately managed by the personal information manager in each study period using the personal information correspondence table and the participant identification number, and not shared with the study-coordinating center, the data center, sample storage center, laboratory test centers, and trial statisticians. The study physicians give the participant's unique anonymization number to the participant and manage the sample specimen with the anonymization number without name, address, telephone number, and so forth. For identification of participants among the study-coordinating center, sample storage center, and laboratory test centers, the anonymization number is used. The sample storage center and the laboratory test centers strictly store and manage the received sample specimen. Study members do not input personal information that can identify patients in the Electronic Case Report (eCRF). Participant identification number is used for identification of individuals among the study-coordinating center, sample storage center, and laboratory test centers. Study physicians use the participant identification number check sheet (supplement 8), recording patient ID at the study site, the participants’ study number, anonymous number, sex, and day of study registration. The participant identification number check sheet is strictly stored within a locked room, formed as the original record by handwriting. In handling of the electronic case report (eCRF), confidentiality of privacy must be considered.

## 11.5 EXPECTED BENEFITS AND DISADVANTAGES

This study is a randomized controlled trial to assess the efficacy of early aggressive intervention (proactive method) with TCSs for infantile AD, compared with conventional treatment for infantile AD based on the Guidelines for the Management of Atopic Dermatitis (2016) (1) (reactive method). There is not enough evidence to show that either one is superior, and the implementation of randomization is under prerequisite that the equipoise of efficacy and safety of both groups exists. Because both interventions are performed daily, there are neither specific benefits nor disadvantages for participants. During the study period, participants can not use TCSs other than trial drugs because they are prohibited as concomitant treatment. Although participants are required to apply to the skin only TCSs that are trial drugs, participants can apply medium, strong, or very strong TCSs, the cost of which is covered for all infants with AD and is not disadvantageous. To reduce the burden of the participants and the proxies (parents or legal guardians), there is saliva sampling without invasiveness. Although the frequency of blood tests is usually within the scope of medical examination, an extra 2.5 mL is collected for laboratory tests and serum preservation. In addition, the proxies (parents or legal guardians) have a duty to write diaries and questionnaires and to bring the rest of the trial drugs. If adverse events related to the trial drugs occur, or study physicians determine that participants need to discontinue their participation, study physicians stop the study immediately, change to different medications, and the participants must obtain a different treatment plan and clinical examinations. The study physicians must ensure the safety and best practice for participants.

# 12 PROTOCOL VIOLATIONS AND DEVIATIONS

A protocol deviation is non-compliance with the approved study protocol related to study treatment, clinical laboratory tests, and so forth. The data center will report any possible deviations that are beyond the applicable deviations defined in the protocol before study initiation to the study-coordinating center. These deviations are categorized as listed below via the steering committee investigation.

## 12.1 VIOLATIONS

A protocol violation is defined as a deviation from the protocol that meets several criteria listed below and is judged as a clinically inappropriate event by investigational sites or investigators listed as follows:

1. impacts on the primary endpoint assessment
2. an intentional or systematic event
3. risky or significantly deviated event.

All violations will be described in the final report in principle when publishing the paper.

## 12.2 DEVIATIONS

12.2.1 UNEXPECTED DEVIATION

Unexpected deviations are not protocol violations (12.1) nor acceptable deviations (12.2.2). If the study physician judges that it is not possible to maintain remission of atopic dermatitis in the standard treatment group, it will be possible to start the same protocol as the early aggressive treatment group later than 8 weeks after enrollment, and such a case is defined as a deviation.

Deviations are described in central monitoring reports. If there are many specific deviations, the results of the deviations will be mentioned in the final report.

12.2.2 ACCEPTABLE DEVIATION

Acceptable deviations are decided by the steering committee, the principle investigator and/or the study-coordinating center under discussion with the data center and defined before and/or after study initiation. Acceptable deviations will not be mentioned in monitoring reports.

# 13 QUALITY CONTROL AND QUALITY ASSURANCE

## 13.1 MONITORING

This study follows the Standard Operating Procedure for monitoring and audit of clinical studies in the National Center for Child Health and Development and for conduct of monitoring to determine that the study is performed safely and in accordance with the protocol. The data from the eCRF are checked by central monitoring. The data center reports regularly on data monitoring results and they are submitted to the principle investigator. The principal investigator submits the report to the Steering Committee, the Independent Data Monitoring Committee, and the head of each facility. As a result of central monitoring, if the principle investigator deems it necessary, on-site monitoring will be carried out. The monitoring system and the implementation plan are described in Supplements 9 and 10.

## 13.2 AUDIT

This study will not be audited.

## 13.3 STORAGE AND DISCARD OF DATA AND SAMPLES

All records about participant's consent, the participant identification number check sheet, data to be entered in the electronic case report (eCRF) (examination data, treatment diary, and so forth), authorization form of the IRB, and recorded documents by the study investigational site are kept by the head of each study investigational site. For the management at the Center for Development and Medical Care, they are kept in a keyed cabinet at the Division of Allergy (Research Building 4th Floor). The storage duration will be 5 years after the study completes or stops. Laboratory test centers will discard all samples as soon as they are tested. The sample storage center will store all serum samples until the samples are used completely, following another study plan. The stored sample at the sample storage center is used according to a separately determined research plan and stored until the end of the retention period of the participant identification number check sheet or until the sample is used up, which ever is earliest.

